## Enzyme activity testing

G6PD activity will be measured using spectrophotometry at the lab maintained by icddr,b for all participants. Samples are transported on a daily basis from the field to the icddr,b lab and results are communicated to the field. A subset of collected samples, tested with spectrophotometry, will be tested with flow cytometry to assess lyonisation at a reference centre capable of performing the respective procedure

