## Molecular testing (host)

Based on availability of funds a subset of samples will be tested for known and unknown variants of the G6PD gene. Genotyping and sequencing will be done at the Sanger Insitute, Uk. Host genotyping is strictly related to the G6PD gene (Xq28) and only to achieve the study objectives.

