## Other Endpoints

- Proportion of patients adhering to 14 days of primaquine treatment in the vivax cohort as measured by Masimo and pill count
- Distribution of G6PD activity among the study population
- Frequency and type of variants of the G6PD gene within the study population

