# Statistical analyses

- Safety data will be presented as summary statistics (including number, mean, median, interquartile range, standard deviation, minimum and maximum) of all vital signs variables (values and changes from baseline) will be calculated for each visit by treatment group.
- G6PD activity will be categorised and the relative risk (RR) of a drop of Hb > 25% between day 3 and 9 and day 3 and 16 and day 23 and 30 will be calculated per category for all participants treated with 14 days of PQ.
- Hematological results will be presented as continuous variable of Hb concentration at Day 0, 3, 6, 9, 12 and 16. The fractional fall in Hb between baseline and day 9 and 16, will be calculated, as well as the proportion of patients with anaemia less than 7g/dl between day 3 and day 9.
- Parasite clearance rate will be defined according to the World Wide Antimalarial Resistance Network guidelines (WWARN)[[20](#_ENREF_20)]. The parasite clearance time (PCT) is defined as the time elapsed between the patient’s first dose and the time of the first negative blood slide.
- G6PD variants detected will be presented descriptively, G6PD activity observed will be displayed in the form of a histogram displaying G6PD activity vs. number of patients.

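### G6PD activity and variants are planned for all patients together, although the gene is X-linked, so the pooled figures depend on the share of men enrolled

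*Protocol*

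**What the plan says.** Two of the endpoints listed under Other Endpoints concern G6PD: "Distribution of G6PD activity among the study population" and "Frequency and type of variants of the G6PD gene within the study population". The first secondary objective on G6PD is the risk of haemolysis associated with activity. The second is the distribution of activity and variants among malaria patients.

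Statistical analyses fixes three outputs:
- Activity: "G6PD activity observed will be displayed in the form of a histogram displaying G6PD activity vs. number of patients".
- Variants: a descriptive presentation. It is not stated whether the denominator is patients or X chromosomes.
- Haemoglobin: activity is categorised, and the relative risk of a fall of more than 25% "will be calculated per category for all participants treated with 14 days of PQ". Cut-offs and reference category are not given.

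No section splits any of these by sex. The laboratory sections do recognise X-linkage. Molecular testing (host) states "Host genotyping is strictly related to the G6PD gene (Xq28) and only to achieve the study objectives", and under Enzyme activity testing a subset of samples "will be tested with flow cytometry to assess lyonisation at a reference centre". The case record form in Annex IX records sex.

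**The concern.** Men carry one copy of the gene and women two, so the activity distribution differs in shape between the sexes. Hemizygous men are either deficient or not. Heterozygous women are mosaics and can read anywhere in between, which is why the protocol plans to study lyonisation. One histogram of all patients is a mixture of two different distributions, weighted by whoever happened to enrol. The same holds for a variant frequency if patients are the unit.

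At stake is how well two named endpoints and a secondary objective can be read. A pooled figure from this site could differ from that of another site, or from the local population, only because more men attended the clinic. For the relative risk, activity category and sex may be partly the same variable, so a crude comparison might not separate them.

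**Working it through.** The protocol states no expected G6PD distribution, relative risk or power for these analyses, so there is no planned figure to reproduce. The check asks how far pooled figures move when only the sex mix changes.

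**Inputs**
- Share of men, *m*: 59.44% in the town (Study Site). The share among patients is not given. I use 50% and 75% as assumed bounds.
- Allele frequency, *q*: not given. Rationale and Aim cites 20–40% as the prevalence of deficiency, not split by sex. I assume *q* = 0.2 and 0.4, and check the other reading below.
- Assumptions: Hardy-Weinberg proportions; hemizygous men and homozygous women are fully deficient.
- Enrolment: about 50 vivax and 160 falciparum patients (Sample Size).

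**Formulas**
- Full deficiency, pooled: *mq* + (1−*m*)*q*²
- Patients with any variant, pooled: *mq* + (1−*m*)[1−(1−*q*)²]
- Per X chromosome: [*mq* + 2(1−*m*)*q*] / [*m* + 2(1−*m*)] = *q*, whatever *m* is

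**Results for *q* = 0.2**

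| Share of men | Full deficiency | Any variant (per patient) | Per X chromosome |
|---|---|---|---|
| 50% | 0.100 + 0.020 = 12.0% | 0.100 + 0.180 = 28.0% | 20% |
| 59.44% | 0.119 + 0.016 = 13.5% | 0.119 + 0.146 = 26.5% | 20% |
| 75% | 0.150 + 0.010 = 16.0% | 0.150 + 0.090 = 24.0% | 20% |

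The two pooled summaries move in opposite directions, each by *q*(1−*q*) times the change in *m*: 0.16 × 0.25 = 4.0 points. For *q* = 0.4 the shift is 0.24 × 0.25 = 6.0 points (full deficiency 28.0% to 34.0%, any variant 52.0% to 46.0%).

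Within sex nothing moves. At *q* = 0.2, full deficiency is 20% of men and 4% of women, and any variant is 20% of men and 36% of women.

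**Other reading of the 20–40%.** If these are pooled prevalences at the town sex mix, *q* is about 0.28 to 0.50. From 50% to 75% men, full deficiency then goes from about 18% to 23% at the low end and from about 38% to 44% at the high end. The pattern is the same.

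**Relative risk.** Suppose, as an assumption, that either all or half of heterozygous women read as intermediate and the rest as normal. At the town mix:
- Intermediate group in 50 vivax patients: 50 × 0.4056 × 2*q*(1−*q*) = 6.5 (*q* = 0.2) or 9.7 (*q* = 0.4) if all do, and half of that if half do. This gives about 3 to 10, all women by construction.
- Men in the normal group if all do: 0.476/(0.476 + 0.260) = 64.7% (*q* = 0.2), or 71.0% (*q* = 0.4). If half do, the share equals the enrolment mix, 59.4%; at an even mix it is 50%.
- Illustration with no G6PD effect and all heterozygotes intermediate: with assumed risks of 10% in women and 5% in men, the relative risk is 0.10/(0.647 × 0.05 + 0.353 × 0.10) = 1.48 at *q* = 0.2, and 1.55 at *q* = 0.4. With the risks reversed it is 0.61 and 0.58. These risks are invented to show direction; the documents give none.

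**The case against.** The best case for the plan is that it asks about malaria patients as they present, so the actual sex mix belongs to the question. That stands: the pooled histogram answers the stated objective and can remain. It would be wrong to say that it answers no defined question. But it cannot be compared across settings or read as a gene frequency without the split.

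The shifts are also modest. A 95% interval around 13.5% with 210 patients has a half-width of about 1.96 × √(0.135 × 0.865/210) = 4.6 points, wider than the 4.0-point shift. The 75% figure has no source. The protocol itself calls deficiency protective against vivax, so Hardy-Weinberg shares are approximate in these patients. All true: the numbers show direction and order of size only.

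Denominators and strata may be set in an analysis plan that is not shown. This matters most for variants: counted per X chromosome, the frequency does not move with the sex mix.

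Three stronger inferences are tempting, and the documents do not support them:
- That the relative risk compares women with mostly men. The protocol names no intermediate category. It withholds primaquine only from severely deficient patients, without a threshold, so men with milder deficiency could fall in the middle category.
- That sex differences in haemoglobin will be read as a G6PD effect. The event is a relative fall from the patient's own earlier value, which largely removes differences in level. No sex difference in the risk of such a fall is documented.
- That the analysis loses efficiency by not adjusting for haemoglobin at the start of primaquine or for parasite density. The day-3 windows already start on the day primaquine starts. The gain formula for adjusting a continuous change does not apply to a relative risk of a binary event or to a descriptive fall.

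**Conclusion.** The concern holds for the activity histogram, and for the variant frequency if it is counted per patient. Both depend on the share of men enrolled, by about 4 points (*q* = 0.2) to 6 points (*q* = 0.4) between 50% and 75% men, under Hardy-Weinberg proportions and an assumed allele frequency. That the pooled distribution mixes two sex-specific ones follows from X-linkage alone and does not need those assumptions.

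For the relative risk, entanglement with sex is possible but unquantified. It turns on undefined cut-offs and an undocumented sex difference in risk, so bias should not be asserted. This is a cheap improvement to two secondary descriptions and one secondary objective. It does not touch the primary objective.

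**What to change.** In Statistical analyses and Other Endpoints:
1. Show G6PD activity separately for males and females. The pooled histogram may stay as an addition.
2. Report variants by sex and per X chromosome (one per male, two per female), and state the denominator. This matters the more because host genotyping covers only a funds-dependent subset, whose sex mix may differ from the cohort's.
3. State the activity categories used for the relative risk, and tabulate the risk of a haemoglobin fall above 25% by category within sex.

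Label item 3 as descriptive. With about 3 to 10 women of intermediate activity expected among about 50 vivax patients, it cannot carry an inference. Under the assumptions above the corresponding cell for men is empty, so no male relative risk for that category could be formed.

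The cost is wording only, since sex and haemoglobin are already on the case record form. The downside is smaller strata and wider intervals for each sex-specific figure.

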# Sample Size

In 2013 a total of 142 vivax cases and 2190 falciparum cases were registered within the district of Alikadam with the majority of cases occurring during and after the monsoon season. The study hospital treated a total of 49 vivax cases and 432 falciparum cases in the same year. As the proposed study will be conducted during the peak malaria season we propose an enrolment target of approximately 50 vivax cases and 160 falciparum cases.

This study is part of a framework of comparable studies working with similar tools as proposed herein. Results for the primary objective will be pooled together with results of other sites to provide reliable results.

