# Background

## Local malaria epidemiology and treatment guidelines

Malaria is endemic in 13 out of 64 districts of Bangladesh, representing a population at risk of about 27 million people. The highest rates of malaria in Bangladesh occur in the Chittagong Hill Districts, and *Plasmodium falciparum* (Pf) is the most prevalent species. Recent data from a cross sectional survey in 2009-2012 found a monthly incidence rate of 0.05/1000 individuals for symptomatic *P. vivax* (Pv) infections and 1.16/1000 for symptomatic *P. falciparum*[[1](#_ENREF_1)]. An earlier survey looking at the overall burden of disease (asymptomatic and symptomatic cases) found a prevalence of 14% for all species combined by microscopy and more than 30% positivity by PCR in Bandarban disctrict [[2](#_ENREF_2)]. In this study *P. falciparum* accounted for 58.9%, *P. vivax* for 13.6%, *P. malariae* for 1.8%, and *P. ovale* for 1.4% of all malaria-positive individuals by PCR. The remaining 24.4% were mixed infections[[2](#_ENREF_2)]. Within the district recent data from the Ministry of Health indicates highest rates in the subdistrict of Alikadam. Malaria is seasonal in the Chittagong Hill Tracks, with the peak transmission between May to October[[2](#_ENREF_2), [3](#_ENREF_3)].

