**Map of Alikadam Subdistrict**

*
[figure not shown]
*

Over the last couple of years Alikadam has continuously reported the highest rates of reported and treated malaria infections:

| **Table: Total Malaria 2013 by sub-districts of the Chittagong Hill districts** | | | | |
| --- | --- | --- | --- | --- |
|  | Pf | Pv | MIXED | Grand Total |
| **Bandarban Sadar** | 500 | 11 | 1 | 512 |
| **Alikadam** | 2190 | 142 | 26 | 2358 |
| **Naikongchari** | 1267 | 15 | 13 | 1295 |
| **Ruma** | 678 | 2 | 2 | 682 |
| **Thanchi** | 1084 | 27 | 1 | 1112 |
| **Lama** | 1382 | 82 | 4 | 1468 |
| **Rowangchari** | 1864 | 5 | 0 | 1869 |
| **Sadar Hospital** | 90 | 1 | 0 | 91 |
| **SMO** | 58 | 0 | 0 | 58 |
| Total | 9113 | 285 | 47 | 9445 |

*Source: Ministry of Health and Family Welfare*

In 2013 the hospital has treated a total of 49 P. vivax cases and 432 P. falciparum cases (Ministry of Health and Family Welfare).

- 1. **Context of project**

This project is embedded into the framework of PROMPT (Primaquine Roll Out Monitoring Pharmacovigilance Tool) hosted by the University of California San Francisco (UCSF), USA, and OPRA (OPtimizing the RAdical cure for vivax malaria) hosted by the Menzies School of Health Research (MSHR), Australia, and is facilitated through the International Centre for Diarrheal Diseases, Bangladesh (icddr,b).

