# Methods

## Study Design

This study is a prospective, observational cohort study actively monitoring the hematologic response, safety and tolerability of routine treatment of *P. falciparum, P. vivax* and mixed malaria infections (*P. falciparum + P. vivax*). The study will be conducted in at a health care facility in Allikadam, in the Chittagong Hill Tracts (CHT), Bangladesh.

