## Study Procedures

All patients attending the health care facility will be screened for eligibility, those fulfilling the inclusion and exclusion criteria will be invited to participate in the study.

After provision of written informed consent (Annex VIII) a brief questionnaire will be filled out (Annex IX). Information on demographic background, known hypersensitivity against any of the study drugs and G6PD deficiency will be collected together with the results of a brief physical exam. Depending on body weight, a maximum of 5 ml of venous blood and a fingerprick will be collected from all participants upon enrolment. Additional diagnostic procedures are detailed below.

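### The target of about 50 vivax patients in six months slightly exceeds the 49 vivax cases the study hospital treated in all of 2013, and no accrual assumptions support it

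*Protocol*

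**What the plan says.** The Sample Size section of the protocol sets the numbers: "we propose an enrolment target of approximately 50 vivax cases and 160 falciparum cases". The only reason given is that the study will run in the peak season. Just before this, the section gives two 2013 counts:

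- For the sub-district: "In 2013 a total of 142 vivax cases and 2190 falciparum cases were registered within the district of Alikadam".
- For the facility: "The study hospital treated a total of 49 vivax cases and 432 falciparum cases in the same year". The Study Site section gives the same hospital figures.

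The Synopsis sets enrolment at six months, and Annex XI shows the same (months 4 to 9). Recruitment is at one place: the Study Design section says "The study will be conducted in at a health care facility in Allikadam", and the Study Procedures section says "All patients attending the health care facility will be screened for eligibility". No second recruiting site, referral route or extension of enrolment is described.

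On season, the Background reports transmission "with the peak transmission between May to October", and the Sample Size section says only that most cases occur during and after the monsoon. Neither gives a percentage. No eligibility or consent rate is stated.

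The Sample Size section closes by saying that primary-objective results will be pooled with other sites. It gives no pooled sample size, and no precision or power for this site.

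**The concern.** The target for six months is one more than the facility's count for twelve. A season cannot contain more cases than its year, so the peak-season argument cannot by itself produce 50 from 49. The Exclusion Criteria then remove further patients: haemoglobin below 8 g/dL, pregnancy or lactation, signs of severe malaria, severe malnutrition, interfering regular medication, body weight below 6 kg. Some patients will also decline.

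Vivax patients make up most of those given 14 days of primaquine. The Statistical analyses section computes the relative risk of a haemoglobin drop above 25% by G6PD category in exactly that exposure group. A smaller vivax cohort gives wider intervals for every site-level proportion in it, and sparse cells once it is split by G6PD category.

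**Working it through.** **Inputs from the protocol.** Vivax target about 50; falciparum target 160; hospital cases in 2013: 49 vivax, 432 falciparum; Alikadam cases in 2013: 142 vivax, 26 mixed (table row "Alikadam | 2190 | 142 | 26 | 2358"); enrolment six months at one facility.

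**Inputs that are assumptions.** Share of annual vivax cases falling in the six months: 50-90%. Share of those eligible, consenting and enrolled (uptake): 70-100%.

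**Step 1. Can the target be reproduced?** The protocol gives no formula. As a share of the hospital's annual count:

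- Vivax: 50/49 = 102%
- Falciparum: 160/432 = 37%

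Expected enrolment = 49 × season share × uptake. Both shares are at most 1, so the 2013 count yields at most 49. The falciparum target is comfortably within supply on the same source.

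**Step 2. Expected vivax enrolment.**

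| Season share | Uptake 70% | Uptake 80% | Uptake 90% | Uptake 100% |
|---|---|---|---|---|
| 50% | 17.1 | 19.6 | 22.1 | 24.5 |
| 70% | 24.0 | 27.4 | 30.9 | 34.3 |
| 80% | 27.4 | 31.4 | 35.3 | 39.2 |
| 90% | 30.9 | 35.3 | 39.7 | 44.1 |

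The range is about 17 to 44. At 100% uptake, reaching 50 needs 50/(49 × 0.9) = 1.13 times the 2013 caseload at a 90% season share, and 50/(49 × 0.5) = 2.04 times at 50%.

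**Step 3. Chance of reaching 50.** Treating accrual as Poisson with the expected number as a known mean:

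| Expected accrual | P(50 or more) |
|---|---|
| 34.3 | 0.7% |
| 39.2 | 5% |
| 44.1 | 21% |
| 49 | 46% |

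**Step 4. Illustrative precision.** With zero events in n patients, the exact two-sided 95% upper limit is 1 − 0.025^(1/n):

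| n | Upper limit |
|---|---|
| 50 | 7.1% |
| 44 | 8.0% |
| 35 | 10.0% |
| 25 | 13.7% |

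From 50 down to 35 or 25 patients the limit grows by 10.0/7.1 = 1.4 to 13.7/7.1 = 1.9 times.

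**Step 5. The group given 14 days of primaquine.** Mixed infections receive the same 14-day course. Scaling Alikadam's 26 mixed cases by the hospital's share of falciparum or of vivax gives 26 × 432/2190 = 5.1 to 26 × 49/142 = 9.0 a year, before seasonal and uptake losses. In the other direction, patients with severe G6PD deficiency receive no primaquine; their share is not given.

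**The case against.** The strongest reply is that the target is approximate and the base is one year's count. Malaria incidence varies from year to year, and the stated May to October peak is itself six months long, so enrolment could coincide with it. With an expected accrual of 49, the chance of 50 or more is 46%. Alikadam as a whole had 142 vivax cases, of which 50 is only 35%, so recruitment beyond the hospital could close the gap. All of this is true, but the protocol describes no such recruitment, and an expected accrual near 49 needs virtually no cases outside the six months and virtually no losses.

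Pooling is the second reply, and much of it stands. The primary side-effects objective is to be answered with other sites' data, so the single-site bound is not its planned precision. Pooling is stated for that objective only and without a pooled size. It is not stated for the secondary objectives, among them haemolysis risk by G6PD activity.

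Several stronger readings are tempting but are not supported:

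- A reader might infer that the design will deliver a specific number such as 25-35, or that reaching 50 is practically excluded. Both depend on seasonal and uptake shares that the documents do not give.
- A reader might say that a promised safety bound is lost. The protocol promises none; the limits above only illustrate what n buys.
- A reader might see inconsistent logic between the two targets. Taking nearly all of the scarce species and capping the common one would be coherent.
- Severe G6PD deficiency might be counted against enrolment. It is not: the case record form records the G6PD result on day 2, after enrolment, and the exclusion is from primaquine. It reduces exposure.
- Whether mixed infections belong to the 14-day primaquine group is already settled by the Study Procedures and Statistical analyses sections: they do.

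**Conclusion.** The concern holds as a feasibility point. The stated vivax size is 102% of the hospital's whole-year 2013 count, to be reached in half a year at that facility, and the protocol's own seasonality statement and exclusions make this implausible. Under assumed shares of 50-90% in season and 70-100% uptake, expected vivax enrolment is about 17-44, all below 50. The direction is firm; the size of the shortfall is not, because both shares are assumptions and 2013 is a single year.

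The consequence is lost precision in site-level and secondary results, chiefly the relative risk by G6PD category in the 14-day primaquine group. The documents do not support the further inference that the primary objective fails, since it rests on pooled data of unstated size.

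**What to change.** In the Sample Size section, take one of two routes:

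- Replace the vivax target with the expected six-month accrual at the facility. State the seasonal and uptake shares assumed, give the exact-interval precision at that number, and describe site-level vivax results as descriptive.
- If patients from the rest of Alikadam's 142 vivax cases are to be recruited, name that source and how those patients reach the study.

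The first route is a text change and needs no extra patients. Its cost is a less favourable stated figure.

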# Ethical considerations

## Data Safety Monitoring Board (DSMB)

A DSMB will be formed at icddr,b to oversee all safty data in regular intervals. The PI in consultation with the IRB Secretariat of icdddr,b will form the DSMB Committee and the frequency of meetings will be agreed on with the Chairman, ERC. It is the principle investigators duty to provide regular reports to the DSMB in due time before the meeting. The DSMB can issue recommendations regarding the further conduct of the study

